##### Test stimulus: mechanical PPT and tolerance

Measurements will be performed 15 min after the TSP measurements. PPT and pressure pain tolerance (PPTo) (kPa/cm²) will be measured at the left and right suboccipital muscles using an electronic pressure algometer (Somedic AB, Stockholm, Sweden).^56^ Pressure will be perpendicularly applied directly on the suboccipital muscles, starting at 0 to maximal 1000 kPa, using a 1 cm² probe with a slope of 30 kPa/s.^17 57^ Participants will be instructed to push the stop button when the sensation of pressure first elicits pain (PPT), and when the maximum amount of pressure that could be tolerated is reached (PPTo). A trial will be performed once on the left shin (tibialis anterior muscle belly, approximately 2.5 cm lateral and 5 cm inferior to the tibial tubercle) before measuring the suboccipital muscles.^58^ Intrarater reliability of tibialis anterior PPT-measurements is good-to-excellent in people with CeH (ICC 0.82–0.92).^59^

Two repeated measurements at baseline, and two measurements parallel with the conditioning stimulus will be performed (figure 3). Averages of the extracted parameters will be used for further analysis.^60^ Test–retest reliability of PPT-measurements at the suboccipital muscles is good to excellent (ICC 0.84–0.93).^61^ Intra-rater reliability of such PPT measurements is moderate-to-good in people with CeH (ICC 0.69–0.87).^17 62^

##### Conditioning stimulus: Cuff pressure algometry

Cuff pressure tolerance (kPa) will be measured at the non-dominant lower leg. A cuff (Nocitech, Aalborg University, Denmark) will be placed around the bare non-dominant calf muscle, mounted with 8 cm distance between its upper border and the tibial tuberosity.^63 64^ Upper and lower borders of the cuff will be marked on the skin to ensure the cuff does not move between stimulations. Pressure tolerance will be determined through the maximal amount of pressure that can be tolerated. Intensity of the cuff pressure for the conditioning stimulus will be predefined as 70% of the pressure tolerance on the non-dominant leg.^63–65^ Computer-controlled cuff algometry (LabBench CPAR+instrument) shows an excellent intrarater reliability (ICC 0.89) in healthy subjects.^66 67^ Test–retest reliability is good (ICCs 0.74–0.87) in healthy subjects.^63^

##### Conditioned pain modulation

CPM will be assessed 3 min after determining cuff pressure tolerance. The pressure (conditioning stimulus) will be kept constant throughout the CPM protocol.^64 65^ Five seconds after inflation of the cuff, PPT and PPTo will be reassessed as described above. Participants will be informed that the conditioning stimulus will be moderately painful, but that they should focus their attention on the test stimulus. The procedure described above will be executed two times sequentially, that is, once with the PPT measurement at the left suboccipital muscles, and once with the PPT measurement at the right suboccipital muscles as test stimulus. A 15 min interval will be provided between the CPM measurements since CPM has a short lasting (<15 min) hypoalgesic effect (figure 3).^68–71^

At the moment, there is no consensus on a normal CPM effect. We propose a method described by Vaegter *et al* to categorise the CPM response as normal or impaired based on the within-subject coefficient of variation (=within-subject SD/within-subject mean) in PPT. Participants will be profiled as having an impaired CPM if the CPM response is less than or equal to the normal within-subject coefficient of variation in PPT between two repeated assessments, and as having normal CPM if the CPM response is greater than the normal variation plus the upper limit of the 95% CI.^60^

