Dynamic protocols, to evoke inhibition or facilitation of pain, have been designed to evaluate endogenous pain modulation and to define a pronociceptive or antinociceptive central pain mechanism. Protocols to assess pain inhibition evaluate the conditioned pain modulation (CPM) paradigm, and pain facilitation assesses temporal summation of pain (TSP).^16^ The term CPM was created for psychophysical protocols that explore diffuse noxious inhibitory control in humans.^19^ The latter manifests as the inhibition of wide dynamic range neuronal activity by descending adrenergic pathways.^19^ CPM is measured by comparing pain induced by a test stimulus, with pain induced by the same test stimulus either during (parallel) or after (sequential) a conditioning stimulus. TSP is a nociceptive mediated process, which is considered to reflect advanced spinal synaptic facilitation in the dorsal horn (ie, behavioural correlate of wind-up).^20 21^ TSP is measured by comparing pain ratings between a single noxious stimulus and repeated equal-intensity noxious stimuli at a specific frequency. A third proxy to examine facilitated central pain mechanisms is widespread hyperalgesia.^22^

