#### Profiling-related outcome—pain profile

Participants will be categorised in four pain profiles based on responses to the TSP and CPM (figures 1–3):

P-P I: pronociceptive (increased TSP/impaired CPM).

P-P II: pronociceptive (normal TSP/impaired CPM).

P-P III: pronociceptive (increased TSP/normal CPM).

P-P IV: antinociceptive (normal TSP/normal CPM).

Each participant with CeH will be categorised into a pain profile per measurement location (TSP at the hand and face, CPM at the left and right suboccipital muscles).^49 50^ Additional presence of widespread pain will be evaluated (figure 4). The paragraphs below contain information on the definitions of increased/decreased TSP, impaired/normal CPM and presence of widespread hyperalgesia.

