### Statistics

Primary analyses will report results relating to outcomes on feasibility. Descriptive statistics and content analysis will be used to assess feasibility of the protocol. The feasibility study will provide useful information with regard to planning, testing study procedures (eg, estimation of the recruitment rate, plausibility of multicentre collaborations, etc), and investigating outcomes to support adequate sample size calculation.^73^ Data from the CMP and TSP measurements will be used to estimate post hoc sample size (G*Power V.3.1.9.4, Kiel Germany) for a larger trial.

Individual PMPs of at least 12 participants with CeH will be mapped based on the methods outlined in the Profiling-related outcome—psychosocial lifestyle profile and conditioned pain modulation sections. Secondary analyses will involve an analysis of proportions (%) of the different psychosocial lifestyle profiles and pain profiles. Currently no data are available in people with CeH, therefore a pragmatic approach is proposed based on the work of Julious who recommended 12 participants as the minimum for pilot studies.^74^ Justifications for this sample size are based on rationale about feasibility and precision about the mean and variance.^74^ Both primary and secondary analyses will be used to decide whether the feasibility study should be expanded to a full-scale study. The latter implies registering of the trial in accordance with the WHO Trial Registration Data Set (V.1.3.1).

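### The CPM rule puts undetectable change and a falling PPT in one pronociceptive class, and leaves responses between its two cut-offs without a profile

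*Protocol article*

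**What the plan says.** The section Conditioned pain modulation acknowledges that "At the moment, there is no consensus on a normal CPM effect" and proposes a rule taken from a cited method. The yardstick is the "within-subject coefficient of variation (=within-subject SD/within-subject mean) in PPT". A participant is "profiled as having an impaired CPM if the CPM response is less than or equal to the normal within-subject coefficient of variation" of two repeated assessments, and is classed "as having normal CPM if the CPM response is greater than the normal variation plus the upper limit of the 95% CI". No value is given for the CV. The text does not say whether it is an external reference figure, an estimate from this study's baselines, or each participant's own figure.

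The pain-profile section crosses CPM with TSP into four profiles. One is "P-P II: pronociceptive (normal TSP/impaired CPM"), so impaired CPM is enough for the pronociceptive label even when TSP is normal. No profile is indeterminate. Under Test stimulus, each CPM response rests on two averaged baseline and two averaged conditioned PPT readings per side. The Statistics section says that "Secondary analyses will involve an analysis of proportions (%) of the different psychosocial lifestyle profiles and pain profiles", and that primary and secondary analyses together inform the decision to expand to a full-scale study.

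**The concern.** A limit built from within-subject variation can indicate whether a change stands out from noise. Failing to exceed it does not show that inhibition is absent. The rule treats that failure as a mechanistic finding: an undecided result becomes impaired CPM and then a pronociceptive profile. Because the cut-off is open below, a clear fall in PPT under the cuff gets the same label. The two cut-offs also do not meet, so some participants cannot be placed in any profile.

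The aim is to identify which pain mechanism is involved, and the profile shares are the secondary result. A reader of the table could not tell how much of the pronociceptive share is evidence of failed or reversed inhibition and how much is measurement that could not decide.

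**Working it through.** The protocol gives no CV, expected share or error rate for this rule, so there is no figure to reproduce. The check is of how the rule behaves.

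**Inputs from the article.** Impaired if response ≤ CV. Normal only above a higher cut-off. Two baseline and two conditioned readings, averaged. "Intra-rater reliability of such PPT measurements is moderate-to-good in people with CeH (ICC 0.69–0.87"); test–retest ICC 0.84–0.93.

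**Assumptions, not in the article.** Total between-person PPT SD of 25–45% of the mean (central 35%); mean true response μ from 0 to 20%; true between-person SD τ = 15%.

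**Plausible CV.** CV = total SD × √(1 − ICC). At 35%, ICC 0.87 gives 35 × √0.13 = 12.6% and ICC 0.69 gives 35 × √0.31 = 19.5%. The test–retest ICCs give 9.3–14.0%. Over 25–45% and all the quoted ICCs the range is about 7–25%.

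**Error of the response.** With 2 + 2 readings, the error SD of the relative change is about CV × √(1/2 + 1/2) = 1 CV. The cut-off is thus one error SD of the response.

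**1. Pooling.** P(impaired) = Φ((CV − μ)/√(τ² + CV²)). At CV 10% and τ = 15% the denominator is √(225 + 100) = 18.0%.

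| μ | Impaired | Of these, within ±1 CV | Of these, below −1 CV |
|---|---|---|---|
| 0% | 71% | 59% | 41% |
| 10% | 50% | 73% | 27% |
| 20% | 29% | 84% | 16% |

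At μ = 10%, 48% of the impaired have a true effect below zero, so about half have some true inhibition. One person whose PPT truly rises 15% is called impaired with probability Φ((CV − 15)/CV): Φ(−0.50) = 31% at CV 10%, Φ(−0.19) = 42% at 12.6%, Φ(0.23) = 59% at 19.5%. Simulation with a noisy baseline in the denominator gives 33%, 43% and 58%.

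**2. Unclassified band.** Suppose the CV is estimated from 12 baseline pairs (12 degrees of freedom). The upper 95% limit is then 10 × √(12/4.404) = 16.5%. The phrase defining normal can be read as that limit (16.5%) or as the CV plus that limit (26.5%).

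| μ | Unclassified, cut-off 16.5% | Unclassified, cut-off 26.5% |
|---|---|---|
| 0% | 11% | 22% |
| 10% | 14% | 32% |
| 20% | 13% | 35% |

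**3. Effect of noise on the impaired share (τ = 15%), as noise goes through 5, 10, 15 and 20%.**

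| CV source | μ = 0% | μ = 10% | μ = 20% |
|---|---|---|---|
| Group CV from this study | 62, 71, 76, 79% | 38, 50, 59, 66% | 17, 29, 41, 50% |
| Fixed external CV of 10% | 74, 71, 68, 66% | 50% throughout | 26, 29, 32, 35% |

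Using each participant's own two baselines at μ = 20% gives 16, 26, 36 and 44%. With a fixed external CV the share moves towards 50%, so its direction depends on μ.

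**4. Which symmetric limit.** With no true effect, a response falls outside ±1 CV with probability 2 × (1 − Φ(1)) = 32%, 16% on each side. Outside ±1.96 error SDs it is 5%. At CV 10%, τ = 15% and μ = 10%, the wider limit (±19.6%) gives 30% inhibition shown, 65% no detectable change and 5% PPT decrease shown. At μ = 20% the split is 51%, 48% and 1%.

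**The case against.** The rule is a disclosed choice from a cited method, made where the article admits there is no consensus. In the article's framework impaired CPM means that inhibition was not shown, and absent or reversed inhibition can both belong there. That stands: this is not an arithmetic error. It does not justify calling an undecided result pronociceptive, and it does not close the gap between the cut-offs.

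Three stronger readings are tempting and are not supported.

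- A reader might infer that noisier measurement always inflates the pronociceptive share. The word normal before the CV also allows a fixed reference value, and then the share can stay flat or fall.
- A reader might take the Introduction's "Dynamic protocols, to evoke inhibition or facilitation of pain" as promising a facilitation class for CPM. The next sentence there assigns inhibition to CPM and facilitation to TSP.
- A reader might infer that every change within measurement error is called impaired. The cut-off is only one SD, so with no true effect and no true between-person spread about 16% still exceed it by chance.

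The consequence is also limited. The classes feed descriptive percentages in about 12 people, and no particular share is tied to the expansion decision. At n = 12 a share of 46% has a margin of about 1.96 × √(0.46 × 0.54/12) = 28 percentage points, larger than many of the shifts above. The article also expects to adapt its outcome analyses after this study. All of this keeps the point modest, but the repair needs no new data.

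**Conclusion.** The point holds on the text alone in two respects. The impaired class has no lower bound and is sufficient for a pronociceptive profile, so undetectable change and a falling PPT are pooled. Responses between the impaired and normal cut-offs have no profile. A third respect is conditional: noisier PPTs raise the pronociceptive share if the CV comes from this study's own readings and mean CPM is inhibitory, and need not do so with a fixed external CV.

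In the illustrative cases with a 10% CV, 59–84% of those called impaired show no change beyond one CV, and 11–35% of all participants are unclassified. These sizes rest entirely on the assumed CV, mean and spread of true effects. Alpha, power and the sample size of 12 are not affected. What changes is what the profile shares can support, including their part in the expansion decision.

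**What to change.** State where the CV comes from, and define the upper cut-off for normal CPM so that it has one reading. For each side, report three shares: inhibition shown, no detectable change (including the band between the present cut-offs), and PPT decrease shown. Use a limit scaled to the error of the averaged response, for example 1.96 times its error SD. One CV on both sides would give about 32% of people with no true effect a directional label.

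List the middle class separately in the pain-profile table rather than counting it as pronociceptive, and give each participant's percentage response beside the limit. Keep the cited classification as a comparison line.

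The cost is a wording change and an extra class in the table, with no new measurements. The downside is that fewer of the 12 receive a definite CPM label and the main table departs from the cited method.

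### The two CPM cut-points leave an interval with no class, so some participants may fit none of the four pain profiles; how many cannot be told from the protocol

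*Protocol article*

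**What the plan says.** The section Conditioned pain modulation sets a two-class aim: "to categorise the CPM response as normal or impaired based on the within-subject coefficient of variation". It defines the yardstick as the "within-subject coefficient of variation (=within-subject SD/within-subject mean) in PPT" and then gives two conditions. A participant has "impaired CPM if the CPM response is less than or equal to the normal within-subject coefficient of variation in PPT between two repeated assessments". A participant is profiled "as having normal CPM if the CPM response is greater than the normal variation plus the upper limit of the 95% CI". Nothing is said about a response that meets neither condition. The same section acknowledges that there is no agreed definition of a normal CPM effect.

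The section Profiling-related outcome—pain profile builds on this rule: "Participants will be categorised in four pain profiles based on responses to the TSP and CPM". The four profiles cross increased or normal temporal summation (TSP) with impaired or normal CPM. It adds: "Each participant with CeH will be categorised into a pain profile per measurement location", with CPM assessed at the left and the right suboccipital muscles.

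The Statistics section says "Individual PMPs of at least 12 participants with CeH will be mapped" and "Secondary analyses will involve an analysis of proportions (%) of the different psychosocial lifestyle profiles and pain profiles". It also says that primary and secondary analyses together will inform whether to go on to a full-scale study.

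**The concern.** A two-class rule should assign every possible value to exactly one class. This rule uses a lower cut-point for impaired and a higher one for normal, and leaves the interval between them empty. A participant with modest inhibition could fall there and belong to none of the four profiles. The four proportions would then not sum to 100%. The people left out would not be a random subset, because they would be the ones with intermediate responses. With 12 participants, each unclassified person moves a proportion by 1/12, about 8 percentage points. If the class were settled only after the data were seen, the choice would be post hoc.

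A second problem concerns the upper cut-point. The protocol does not say which quantity the 95% CI belongs to. If it is the CI of the CV, its upper limit already lies above the CV, and adding that limit to the CV would count the variation twice.

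**Working it through.** The protocol gives no numerical cut-point and no expected share per class, so there is no figure to reproduce. The check has a logical part, which needs no assumptions, and a numerical part, in which every input is assumed.

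**1. Is there a gap?** Let x be the CPM response and U the upper 95% limit.
- Impaired: x ≤ CV.
- Normal, reading A (literal addition): x > CV + U. The gap is (CV, CV + U].
- Normal, reading B (the cut-point is U itself, taken as the upper limit of the CI of the CV): x > U. The gap is (CV, U].

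Both intervals are non-empty, because an upper confidence limit of the CV exceeds the CV. None of the four profiles has a place for a response in the gap.

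**2. How far apart are the cut-points?** Assume the CV comes from n people with two readings each. An approximate chi-square limit is U = CV × √(n / χ²₀.₀₂₅,ₙ). Under reading A the ratio of the normal to the impaired cut-point is 1 + U/CV.

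| n (assumed) | U if CV = 10% | CV + U | Ratio, reading A |
|---|---|---|---|
| 12 | 16.5% | 26.5% | 2.65 |
| 20 | 14.4% | 24.4% | 2.44 |
| 50 | 12.4% | 22.4% | 2.24 |
| 100 | 11.6% | 21.6% | 2.16 |

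Under reading A the ratio is above 2 whatever n is, because U > CV.

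**3. What share could fall in the gap?** Assume the CPM response, as a percentage of baseline PPT, is normally distributed with mean m and SD s. With Φ the standard normal distribution function, the share is Φ((upper cut − m)/s) − Φ((CV − m)/s).

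Worked case: CV 10%, n = 50, m = 10%, s = 20%.
- Reading A: Φ(0.62) − Φ(0) = 0.733 − 0.500 = 0.233.
- Reading B: Φ(0.12) − Φ(0) = 0.548 − 0.500 = 0.048.

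The full grid has 4 × 4 × 4 × 3 = 192 scenarios: n = 12, 20, 50, 100; CV = 5, 10, 15, 20%; m = 0, 10, 20, 30%; s = 15, 20, 30%.

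| Unclassified share per site | Reading A | Reading B |
|---|---|---|
| Minimum (n 100, CV 5%, m 30%, s 15%) | 5% | 0.6% |
| Median over the grid | 21% | 6% |
| Maximum (n 12, CV 20%, m 30%, s 15%) | 69% | 33% |
| Scenarios with share above 10% | 86% | 25% |
| Expected number of 12 at the median | 2.6 | 0.7 |
| P(at least one of 12) at the median, 1 − (1 − p)¹² | 0.945 | 0.51 |

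The grid medians summarise the chosen scenarios. They are not estimates for this population.

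**The case against.** Five points can be made for the protocol.

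- **A grey zone between clear impairment and clear normality is a defensible design.** This stands as a general point. But the profile scheme would then need a place for it and the proportions would have to report it, and the text does neither. Figures 1 and 3 are not available here; the text mentions no third CPM class.
- **The rule is attributed to a published method, and an article condenses.** The source cannot be checked here, and the wording may be a loose rendering of it. But this is not a detail left to another document: the article states the rule, and the stated rule does not do what it is introduced to do.
- **Double counting is not proven.** This stands. A reader might infer that the variation is certainly counted twice. That holds only if the interval is the CI of the CV and the addition is literal. The text settles neither.
- **Comparing a response with a CV already implies a relative scale.** Largely accepted. Stating the formula is a clarification, not a separate fault.
- **Little is lost in a feasibility study.** The primary outcome is feasibility, the profile proportions are descriptive, and the Design section foresees adapting the analyses. The CPM data are kept and can be reclassified. This lowers the severity but does not make the rule workable.

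A reader might also infer that fewer than 12 profiles will be mapped. The documents do not support that as a firm consequence. Twelve is a minimum, profiles are assigned per location so an unclassified response on one side need not affect the other, and the psychosocial lifestyle profile does not depend on CPM.

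**Conclusion.** The concern holds in a limited form. It is certain from the text that the CPM classification is not exhaustive, and that this conflicts with placing each participant in one of four profiles and analysing their proportions. It is also certain that the referent of the 95% CI is unstated. If it is the CI of the CV and the addition is literal, the normal cut-point is more than twice the impaired one.

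It is not established that many participants will be affected, although a reader might infer that. The documents give no CV, CI, or mean and SD of the CPM response. Under the assumed inputs the unclassified share per site is roughly 5–69% (median about 21%) on the literal reading, and roughly 1–33% (median about 6%) if the cut-point is the upper limit itself. The supportable statement is that some participants may be unclassifiable at a site, in an unknown number.

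This should be fixed, but it does not threaten the study: the outcome is secondary and descriptive, and the remedy is a matter of wording.

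**What to change.** Before analysis, make the CPM classification exhaustive in one of two ways.

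1. **One cut-point.** Impaired if the response is ≤ T, normal if > T, with T stated in advance as either the CV or its upper 95% limit. Report the number of participants between the two values as a sensitivity analysis.
2. **An intermediate class.** Name it, add it to the pain profiles, and include it in the reported proportions.

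With either option, state that the 95% CI is that of the CV and is not added to it. Also state the scale: CPM response = 100 × (mean PPT during conditioning − mean baseline PPT) ÷ mean baseline PPT.

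**Cost.** A few sentences and no extra measurements. Either option leaves 0% unclassified by construction, but each has a drawback.

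- A single cut-point assigns borderline responders by one line and shifts the split. For illustration, assume a response with mean 15% and SD 20%, CV 10% and U 13–16.5%. The literal rule gives 40% impaired, 28–34% normal and 25–32% unclassified. T = U gives 46–53% impaired and 47–54% normal. T = CV gives 40% impaired and 60% normal. The documents give no ground for preferring one T, so the choice must be made and recorded before the data are seen.
- An intermediate class raises the number of profiles from 4 to 2 × 3 = 6, an average of 12/6 = 2 participants per profile at a site.
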